## 6.0 INTERVENTION: Task-Shifting Depression Care Models

### 6.1 Protocolized Model

Drawing from collaborative care models of depression treatment such as Partners in Care, MANAS and STAR\*D, the protocolized model implements an algorithm-based, nurse-driven approach to administering depression diagnosis and antidepressant therapy. While other collaborative care models incorporate psychotherapy and reserve antidepressants for severe depression, our model focuses solely on the use of antidepressants. We believe that use of medication requires relatively less trained resources and personnel time than would be needed to add a form of psychotherapy, resulting in a more reliable and scalable treatment for resource constrained settings. The components of the protocolized model are outlined below and summarized (in comparison with the clinical acumen model) in Table 1.

***Routine depression screening:*** All adult clinic patients will be screened for depression at each clinic visit using the first two items of the Patient Health Questionnaire (PHQ-2), administered at the triage station (along with measurements of body weight, blood pressure, pulse and elicitation of presenting health problems) by expert clients or VHT workers. The PHQ-2 assesses depressed mood and loss of interest; patients who screen positive for depression (3+ scores; range: 0-6) will be referred to the nurse in the protocolized model for further depression evaluation if medically stable; in the clinical acumen model, PHQ-2 data are relayed to the primary care provider. Medical stability is defined as not about to start (or recently started) ART or treatment for an acute opportunistic infection (see Figure 1). Further evaluation is deferred for medically unstable patients until their condition and treatment is stable, as mood may improve once they are medically stable, and starting antidepressants simultaneously with other medical treatments would complicate side effect and response evaluation. However, depressed patients who are medically unstable will be evaluated for suicide risk and the need for immediate treatment.

***Depression diagnosis:*** Further evaluation of patients who screen positive for depression and are medically stable will be conducted using the full 9-item Patient Health Questionnaire (PHQ-9). Patients who score greater than 9 on the PHQ-9 (range: 0 to 27), which has been shown to correspond highly with Major Depression as determined by a diagnostic interview, will be further assessed using the criteria for Major Depression on the Mini Neuropsychiatric Interview (MINI; 5 symptoms scored as 3 on the PHQ-9, at least one of which is depressed mood or loss of interest). Providers are trained to further assess antidepressant eligibility using the MINI screening items for bipolar disorder, psychosis and substance abuse, as well as medical contraindications (e.g., pregnancy or breast feeding, seizure disorder); for patients with these conditions, the supervising psychiatrist will be consulted to determine appropriate treatment.

***Prescription of antidepressants:*** If eligibility for antidepressant therapy is confirmed, the provider (nurse in the protocolized model and primary care provider in the clinical acumen model) will educate the patient about depression as a disease, and antidepressant treatment, including: prognosis, the goal of symptom remission, that treatment often takes 2-3 weeks to have an effect, and that side effects are generally minor and temporary. Helping the patient to understand the treatment is intended to encourage adherence to treatment. The patient will then receive a prescription and supply of either fluoxetine or imipramine prior to departing the clinic, which the provider will select based on the patient's presenting symptoms and psychiatric history; fluoxetine will be prescribed unless the patient presents with insomnia, sexual dysfunction or history of Bipolar disorder. Fluoxetine has been shown to have some drug interactions with HIV protease inhibitors, but protease inhibitors are rarely used in Uganda.

**Monitoring of treatment response and side effects:** After treatment prescription, the patient will return to see the prescribing provider two weeks later for monitoring of side effects, treatment response and any need for change in dosage or medication. The visit schedule will then become monthly until the patient has been in remission (defined as PHQ-9 < 5 and tolerating any side effects) for one month, at which time the visit schedule will be modified to match the patient's HIV care visit schedule (typically every 2-3 months), but no less than every 3 months; if the patient experiences a relapse, visits will return to monthly until in remission. At each visit, the provider will assess depressive symptoms (using the PHQ-9), presence of side effects and strategies for managing such symptoms, as well as enquire about medication adherence. Psychoeducation regarding depression treatment will continue and be emphasized as needed. A Depression Treatment Registry will be instituted at each site in which the above listed parameters are recorded for each visit, as well as medication and dosage prescribed. These data will be reviewed during supervision and used for reference in future follow-up visits, as well as for tracking fidelity to the treatment protocol.

Starting daily dose is 20 mg for fluoxetine and 50 mg for imipramine; imipramine will increase to 75 mg after one week. Patients remain on this low dose until their second follow-up visit (Week 6), at which time the determination of the need for a change in dose or medication will be considered based on measures of depressive symptoms and side effects (see Figure 2). *For patients tolerating any side effects:* dose will remain the same if they are fully responsive to treatment; for partial responders, the provider will decide whether to maintain the dose or increase by one increment (add 20 mg of fluoxetine or 25 mg of imipramine); nonresponders will have their dose increased by one increment. *For patients not tolerating side effects:* if a full or partial response to treatment, the current dose may be maintained and side effects addressed (with pharmacologic or other types of strategies) or the provider may reduce the dose or change the antidepressant; for nonresponders, the antidepressant will be changed.

This algorithm-based treatment decision process is repeated at each monthly visit until the patient is fully responding and in remission-- the medication dose will then remain the same (unless subsequent changes are needed due to side effects or relapse). Maximum dose is 80 mg/day for fluoxetine and 300 mg/day for imipramine. If patients don't respond to or tolerate fluoxetine or imipramine, amitriptyline is an option; alternatively, a medication that is being partially responded to may be continued in hopes that response will improve over time. Concomitant medications for associated symptoms such as sleep disturbance, anxiety or agitation, or side effects (e.g., sexual dysfunction), may be used and will be documented.

**Treatment discontinuation:** Once the patient has been in remission for at least 6 months, treatment will be discontinued, unless the patient has a history of multiple episodes of Major Depression, in which case treatment will be maintained for two years. If on treatment at end of study, treatment will be maintained as part of usual care. Drug supply is purchased by the study to ensure no drug stock outs, but both medications are available free of charge to the clinics through the Ministry of Health.

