**Start-up Training:** Training will start with the study's lead investigators and psychiatrists conducting an intensive one-day training workshop with the clinic staff (expert clients/VHTs, nurses, clinical/medical officers) to train them on the structure and goals of the study, and each component of the treatment model. One workshop will be held for the clinics in the protocolized arm, and a separate workshop for those in the clinical acumen arm. All nurses and clinical/medical officers at each site will be trained so that duties can be evenly spread, to build overall capacity for depression care, and to mitigate against the effects of occasional staff transfers. Training will consist of didactic instruction, interactive role-playing, and small breakout group discussions. Following the workshop, tools to facilitate implementation of the model (laminated copies of the PHQ-2 for the triage station, and PHQ-9/MINI for each nurse/prescribing provider, Depression Treatment Registry, psychoeducation posters and flipcharts) will be delivered to each site, and supervising psychiatrists will be on-site one day a week for 4-6 weeks (until both the supervisor and nurse are comfortable with the nurse's competency in implementing the protocol) to provide training and mentorship (e.g., sitting in on and co-conducting assessments), after which ongoing on-site supervision will become monthly.

**Ongoing Supervision:** Supervision will be conducted in one-on-one sessions between the site supervisor and each nurse (protocolized arm) and primary care provider (clinical acumen arm), as well as group meetings with all clinic staff involved with implementation of depression care at the site. Furthermore, the supervisor will be available 24/7 for emergency or suicide crisis consultations. During individual supervision, the providers will present new treatment cases since last supervision and problematic or nonresponding cases, allowing the supervisor to discuss the patient's presenting symptoms and the treatment plan for the patient, including side effect management and dose change recommendations. Clinical notes from the Depression

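### Sections 6.1 and 11.2 place the protocolized arm's second follow-up visit, and with it the first dose or drug decision, two weeks apart, and the hold before that visit has no side-effect exception

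*Protocol*

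**What the plan says.** In Section 6.1, the part on monitoring treatment response and side effects has the patient return to the prescriber "two weeks later for monitoring of side effects, treatment response and any need for change in dosage or medication". Visits are then monthly until remission has lasted one month.

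The next paragraph gives the doses: "Starting daily dose is 20 mg for fluoxetine and 50 mg for imipramine; imipramine will increase to 75 mg after one week". It continues: "Patients remain on this low dose until their second follow-up visit (Week 6), at which time" the need to change dose or medication is considered, using both symptoms and side effects, with Figure 2 as the reference. The rules for patients who do not tolerate side effects follow from there. With a full or partial response the dose may be kept and the side effects managed, or "the provider may reduce the dose or change the antidepressant; for nonresponders, the antidepressant will be changed".

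A later hold, once the patient is fully responding and in remission, is worded differently: "the medication dose will then remain the same (unless subsequent changes are needed due to side effects or relapse").

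Section 11.2 gives the monitoring schedule for the same arm as treatment baseline, week 2, week 4, and monthly after that until response. It adds that, when side effects are reported, the depression care manager (DCM) and the primary care provider decide on reducing or discontinuing the drug, following the treatment model protocol.

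**The concern.** There are two linked defects of wording.

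The first is a date. Section 6.1 ties the first dose or drug decision to the second follow-up visit, so the date of that visit is the start of the dosing algorithm for every treated patient in the protocolized arm, including nonresponders waiting for an increase. The two sections give different dates.

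The second is the hold itself. One sentence makes week 2 a visit at which a needed change is looked for. The next paragraph keeps patients on the low dose until the second visit and places reduction and switching for intolerance there. The later hold has a side-effect exception and the early one does not.

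The wording matters more than usual because the structured algorithm is what separates this arm from the clinical acumen arm, and Section 6.3 says that managing antidepressants is new to the clinic staff. Supervisors also review charts for appropriate dosing (Section 6.3) and log how many patients were correctly dosed (Section 7.0). Under the present text, a reduction for intolerance at week 2, or an increase at week 4, could be scored as correct or as a departure.

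**Working it through.** **Inputs.** From Section 6.1: first follow-up at week 2, monthly visits after that, second follow-up labelled Week 6, fluoxetine at 20 mg with a 20 mg increment, imipramine at 75 mg from the end of week one. From Section 11.2: follow-up visits at week 2 and week 4, then monthly.

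**Step 1: reproduce the plan's own date.** Week 2 plus one month (about 4 weeks) = week 6. Section 6.1 is consistent with itself.

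**Step 2: compare with Section 11.2.** Treatment baseline is the prescribing visit, so the follow-up visits are week 2 (first) and week 4 (second). Difference between sections: 6 − 4 = 2 weeks.

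**Step 3: length of the hold after week 2, read literally.**
- Section 6.1 schedule: 6 − 2 = 4 weeks.
- Section 11.2 schedule: 4 − 2 = 2 weeks.
- With a side-effect exception: 0 weeks.

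**Step 4: what the hold defers.** The intolerance rules in Section 6.1 list keeping the dose with management of the side effects, reducing it, or changing the drug. Stopping is not among them. For fluoxetine, one increment below the starting dose is 20 − 20 = 0 mg, so no lower step exists and the literal hold bears on switching only. Imipramine has a lower step: 75 − 25 = 50 mg with the increment in the Section 6.1 text, or 75 − 50 = 25 mg with the one in the Figure 2 footnote. That difference in increment is a separate matter; a lower step exists either way.

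**Step 5: can the hold be read as covering increases only?**
- For: the week-2 visit has the stated purpose of finding a needed change, and the phrase about the low dose follows directly on the starting doses, which is titration language.
- Against: the deferred decision covers the drug as well as the dose, rests on side effects as well as symptoms, and introduces the only detailed rules for patients who do not tolerate treatment.
- Comparison: where a side-effect exception to a hold was wanted, Section 6.1 states it, as in the remission hold.

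The increases-only reading is the more likely intent, but the sentence does not say it.

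**The case against.** The strongest reply is that the protocol already permits early action. The week-2 purpose clause can be read with the hold so that routine titration waits and a needed change does not. Several other passages point the same way, and none carries a time limit:
- Section 6.1: "If patients don't respond to or tolerate fluoxetine or imipramine, amitriptyline is an option".
- Section 6.3: "the providers will present new treatment cases since last supervision and problematic or nonresponding cases", and the supervisor discusses the treatment plan, "including side effect management and dose change recommendations". Supervision is weekly for the first 4 to 6 weeks at a site and monthly after that.
- Section 11.1: if a drug interaction becomes evident, the provider considers modifying the dose or changing the drug.
- Section 11.2: the DCM and the primary care provider decide on reduction or discontinuation, and patients can reach their provider by phone in an emergency at any hour.
- Section 11.5: side effects are relieved by lowering the dose and, if needed, stopping.

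Much of this stands, and it keeps the safety side small. A reader might infer that an intolerant patient must stay on the drug until Week 6. The documents do not support that: stopping is never among the options that the hold defers, and Sections 11.2 and 11.5 allow it at any time. A reader might also work out an average wait from the monthly supervision interval. That is not supported either, because supervision is weekly at start-up and the Section 11.2 decision need not wait for a supervisor.

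The reply leaves two things unsettled. None of these passages says that the hold does not apply to intolerance, and the Section 11.2 clause refers back to the treatment protocol, where the hold and the week-2 clause both sit. Nor does the reply touch the Week 6 and week 4 dates. Figure 2 and the training manual are not available here and may be clearer, so the point concerns the written text only.

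**Conclusion.** The point holds in a limited form. The contradiction in the date is plain: Week 6 in one section and week 4 in the other, 2 weeks apart, for the visit at which the dosing algorithm begins. The hold is imprecise rather than unsafe. Taken literally, it postpones reduction or switching for intolerance by 4 weeks (Section 6.1) or 2 weeks (Section 11.2) after week 2, against a likely intent that only increases for lack of response should wait.

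These lengths rest on the scheduled visit dates and on a nurse applying the hold sentence word for word. The protocol gives no rate of early intolerance, so no count of affected patients can be offered. Severity is minor. The Aim 1 analyses and the power calculation do not depend on it.

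**What to change.** 1. Choose one date for the second follow-up visit, use it in both Section 6.1 and Section 11.2, and check Figure 2 against it.
2. Add an exception to the hold sentence in Section 6.1, modelled on the one for the remission hold: *unless changes are needed due to side effects*. From week 2 the provider can then keep the dose and manage the side effects, reduce it, or change the drug.
3. Say that the automatic change of drug for nonresponders who do not tolerate treatment is not applied at week 2. Section 6.1 itself tells patients that an effect often takes 2-3 weeks, so lack of response at that visit means little.

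The cost is one date, one clause and one sentence; the week-2 visit already exists. The downside is a few early changes for side effects that would have passed, since Section 11.1 says they often do. Keeping the option to hold the dose and manage the symptoms limits this.

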Treatment Registry will be used in the case reviews. Goals of treatment for the individual patient will be discussed and recorded for review at subsequent supervision sessions. The group meetings will provide an opportunity for the clinic staff to work as a team to trouble-shoot any challenges that arise, share experiences and provide peer support to each other in managing depressed patients, which can be taxing emotionally as well as fulfilling.

**Monitoring Fidelity:** Ongoing supervision and review of cases is our primary mechanism for monitoring the fidelity of the implementation of the treatment models. At each monthly supervision, supervisors review the charts of all patients prescribed antidepressants within the past month, as well as 10 randomly selected charts of patients receiving ongoing antidepressant treatment monitoring. The charts will be reviewed for whether diagnosis, symptoms and side effect assessment, and dosing were appropriately performed, and if the patient returned for follow-up visits. Results will be aggregated and monitored on a monthly basis, as well as used to inform the target areas for supervision.

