## 7.0 DATA SOURCES

To evaluate the two task-shifting models, we will compare the implementation, effectiveness, and cost-effectiveness of these models over a 24-month period. Using the RE-AIM framework, we will evaluate the *reach* of depression screening and treatment, *adoption* of depression treatment knowledge and intervention by providers, *quality of implementation* (fidelity to depression care model), and *effectiveness* of depression treatment on patient outcomes. As outlined in Table 2, these implementation domains and corresponding outcomes will be assessed from data triangulated from these data sources: (1) data abstracted from data collection mechanisms integrated into routine care; (2) monthly logs summarizing chart abstracted data completed by the supervising psychiatrists; (3) survey data from a longitudinal cohort of randomly selected patients at each site who screen positive for potential depression (PHQ-9 > 2); and (4) survey data from longitudinal cohort of providers involved in provision of depression care at each site. Survey data from the patient cohort will also be used to assess how change in depression is related to key economic and public health outcomes. These data sources are described in more detail below.

**Routine data abstraction:** We will assess the implementation of screening (% of adults screened; % screened who screen positive) by abstracting data from the Triage Book, which the triage station at each site uses to list the clients who attend each day of the clinic, their vital signs, and PHQ-2 score. PHQ-9 and MINI administration data will be recorded in the patient's clinic chart. Depression Treatment Registry books will be installed at each site for providers to document clients who have started antidepressant therapy and their depression diagnosis, and records of each follow-up visit that include PHQ-9 score, presence of side effects and medication and dose prescribed.

**Supervision log data:** From the chart reviews that the supervisors conduct each month at each site, monthly aggregate scores are recorded for newly prescribed patients (number with correct diagnosis, correct prescribed antidepressant, and correct prescribed dosage) and patients in ongoing treatment (number correctly assessed for depressive symptoms and side effects; number correctly dosed; and number who returned for scheduled follow-up visit in past month).

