**Data Integrity.** Identifying information including subject's name, address, and phone number will be entered on a tracking form, stored separately from all research data, and kept in a locked file cabinet at the study site. The hand-held computer devices used to administer the computer-assisted personal interviews (at baseline and Months 6 and 12) will not collect any identifying information; only the study ID number and patient initials will be entered into these devices. The data on these hand-held computers will be password-protected and data will be uploaded to a study desktop computer on a daily basis. All paper files are stored in locked file cabinets, and electronic files are stored in password-protected files. Furthermore, both paper and electronic files will be identified only by a participant's ID number. Identifying information linking participants to their study ID number will be retained in a locked cabinet.

Figure 1: Depression and Treatment Eligibility Assessment Protocol

[figure not shown]

Figure 2: Algorithm for Dose or Medication Changes

[figure not shown]

\* One increment: fluoxetine = 20 mg/day; imipramine = 50 mg/day

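### One imipramine dose increment is 25 mg in Section 6.1 but 50 mg/day in the footnote of Figure 2, which Section 6.1 cites for the same dose decision

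*Protocol*

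**What the plan says.** Under the monitoring heading of Section 6.1, the Protocol describes how dose is decided at the second follow-up visit and at each monthly visit after that, and points to Figure 2. Two groups of patients who tolerate side effects can have the dose raised:

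- Partial responders, at the provider's choice: "for partial responders, the provider will decide whether to maintain the dose or increase by one increment".
- Nonresponders, as a rule: "nonresponders will have their dose increased by one increment".

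The size of the step is given there as "add 20 mg of fluoxetine or 25 mg of imipramine". On the imipramine starting dose of 50 mg, the same section says "imipramine will increase to 75 mg after one week". The maximum is 300 mg/day for imipramine and 80 mg/day for fluoxetine.

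The Figure 2 image is not reproduced in the text at hand, but its footnote is, at the end of the Protocol: "One increment: fluoxetine = 20 mg/day; imipramine = 50 mg/day".

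Section 6.3 makes dosing part of fidelity monitoring: "The charts will be reviewed for whether diagnosis, symptoms and side effect assessment, and dosing were appropriately performed". Each month this covers all new prescriptions and "10 randomly selected charts of patients receiving ongoing antidepressant treatment monitoring". Section 7.0 then lists "number correctly dosed" among the monthly counts logged at each site for patients in ongoing treatment.

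**The concern.** The same term, one increment, has two values for the same drug in the same algorithm. The protocolized model is defined by its algorithm and is delivered largely by nurses in clinics that had no depression care before the study, so a dose rule with two values is a defect in the description of the intervention itself.

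Two things are at stake. First, prescribing: a nurse working from the text and one working from the figure would give different doses to the same patient, and the difference can grow because the decision recurs monthly. Second, measurement: fidelity is one of the four parameters in the primary objectives of the Study Overview. A supervisor reviewing a chart in which imipramine went from 75 to 100 mg, or from 75 to 125 mg, could call either one right or wrong depending on which statement was in hand.

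**Working it through.** There is no sample size or power figure to reproduce. The check compares the two statements and works out the doses that follow.

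**Inputs**

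| Item | Value | Place in Protocol |
|---|---|---|
| Imipramine increment, text | 25 mg | Section 6.1 |
| Imipramine increment, figure | 50 mg/day | Figure 2 footnote |
| Fluoxetine increment | 20 mg in both | Section 6.1; Figure 2 footnote |
| Imipramine dose before the first response-based step | 75 mg | Section 6.1 |
| Imipramine maximum | 300 mg/day | Section 6.1 |
| Fluoxetine start and maximum | 20 and 80 mg/day | Section 6.1 |

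**Could the two statements be compatible?** A per-dose versus per-day reading fails: Section 6.1 states its starting doses as daily doses, and the fluoxetine step is 20 mg in both places. The missing image does not explain the conflict either, since the footnote is legible and follows the Figure 2 caption. Both statements stand in the current text.

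**First step from 75 mg**

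- Section 6.1: 75 + 25 = 100 mg; 25/75 = +33.3%.
- Figure 2 footnote: 75 + 50 = 125 mg; 50/75 = +66.7%.
- Difference: 125 − 100 = 25 mg; 125/100 = 1.25, so the higher dose is 25% above the lower.

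**Repeated steps.** After k increases the dose is 75 + 25k or 75 + 50k.

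| Increases | 25 mg step | 50 mg step | Ratio |
|---|---|---|---|
| 1 | 100 | 125 | 1.25 |
| 2 | 125 | 175 | 1.40 |
| 3 | 150 | 225 | 1.50 |
| 4 | 175 | 275 | 1.57 |

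A fifth 50 mg step would give 325 mg, above the maximum.

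**Which value is intended?** With 25 mg, (300 − 75)/25 = 9 steps, which lands exactly on the maximum. With 50 mg, (300 − 75)/50 = 4.5, which does not. The early rise from 50 to 75 mg is also a 25 mg step. Both facts favour 25 mg, but that early rise is initial titration and not a response-based step, and a maximum need not be a whole number of steps away. For fluoxetine, (80 − 20)/20 = 3 steps under either statement.

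**Visit schedule (minor).** Section 6.1 has the first follow-up at two weeks and the second at week 6, then monthly visits until one month in remission. Section 11.2 has visits at week 2 and week 4, then monthly until response. The second visit differs by 6 − 4 = 2 weeks. Section 11.2 attaches no dose decision to week 4.

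**The case against.** The strongest reply is that the conflict is real but small.

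- **Reach on outcomes.** Section 2.0 lists treatment uptake and depression reduction as the Aim 1 comparisons and does not mention fidelity; Section 9 gives fidelity no power calculation or analysis. Only imipramine patients whose dose was raised are affected, in one of several supervision counts. This stands, and it limits the weight of the point. It does not remove it, because the Study Overview does name fidelity among the primary objectives.
- **Clinical safeguards.** Supervising psychiatrists discuss nonresponding cases and dose changes with providers, symptoms and side effects are checked at every visit, and both 100 and 125 mg are far below the maximum. This also stands: no harm to patients is shown. But supervision cannot judge a dose against a rule that has two values.
- **The training manual.** Providers hold a manual that is not shown, and it may give one value. The conclusion is therefore about the Protocol as written, not about what was done in the clinics.
- **Scope by arm.** The increment belongs to the protocolized model. The Protocol does not make clear whether dosing in the clinical acumen clinics is judged against the same steps, so the problem may concern five clinics rather than ten.
- **The visit schedule.** Section 8.0 defines full response in the same terms that Section 6.1 uses for remission. If Section 11.2 means full response, the two end points for monthly visits differ only by the extra month in remission. That part of the minor item is weak; the week 4 versus week 6 difference remains.

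**Conclusion.** The concern holds. The Protocol gives two values, 25 mg and 50 mg/day, for one operative dose rule, and it offers no way to choose between them. The size is 25 mg at the first step (100 versus 125 mg) and 100 mg after four full steps (175 versus 275 mg), for patients who start from 75 mg, tolerate the drug and are raised at each decision.

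It should be fixed, because the step is required for tolerating nonresponders, can recur monthly and feeds a logged fidelity count. It does not threaten the trial's main comparison. The share of patients on imipramine is not stated, so the number affected cannot be estimated; fluoxetine is the default, with imipramine for those with insomnia, sexual dysfunction or a history of bipolar disorder. That 25 mg is the likelier intention is an inference, not something the Protocol settles.

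**What to change.** - Have the clinical leads confirm one imipramine increment and state it identically in Section 6.1 and the Figure 2 footnote.
- Check that the training manual gives the same value, and remind providers at the next monthly supervision.
- Score the dosing item in the supervision log against the confirmed value, and say whether that standard applies in both arms.
- Align Section 11.2 with Section 6.1: week 2, week 6, monthly until one month in remission, then at least every 3 months. If a week 4 safety visit is wanted, add it to Section 6.1 and say whether dose is decided there.

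The cost is one corrected line for the increment, one corrected sentence in Section 11.2, a short statement on scoring, a manual check and a supervision reminder. Design, sample size and analysis do not change.
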